### Other variables

Preoperative: age (years), body mass index (BMI) (kg/m2), smoking (packets/year), Charlson comorbidity index (CCI), previous pelvic surgeries, previous radiotherapy, Briganti criteria (low /intermediate/high risk), total testosterone levels (ng/dL). Characteristics of the tumor: height of the lesion (cm) by rectoscopy, location of the tumor (anterior, posterior, right or left lateral), cTNM staging.

#### Surgical

Type of surgical technique (LAR, NOTES-hybrid), surgical time.

#### Postoperative

Morbidity at 30 days (according to the Clavien-Dindo classification [32]), 30-day mortality, CCI [33], hospital stay. Definitive pathological anatomy: Size of the lesion (mm), pTNM and the completeness of mesorectal excision,according to the Quirke classification.

### Statistical analysis

#### Sample size

With an α risk of 0.05 (5%), a one-sided hypothesis and a βriskof 0.1 (power of 90%), taking into account that the prevalence of post-TME sexual dysfunction is 50% and intending to reduce the figure to 20%,it will be necessary to include 41 patients in the two groups. Estimating a possible loss to follow-up of 10%, the total sample required will be 90 patients: 45 per group.

In our hospital rectal surgery for cancer is expected between 60 and 70/year, with inclusion criteria, we think that about 45–50 could be included. That means, that probabibly in two years, the recruitment should be finished.

#### Analysis of patients by intention to treat, per protocol, and patients lost

Patients will be analysed by intention to treat (ITT), per protocol, andlost patients.

The intention to treat analysis will be applied to all randomized patients.

The per protocol analysis will include part of the group in which direct dissection of the IMA is performed, and all the group that undergo dissection from the IMV to the IMA. Statistical analysis of the lost patients will be performed.

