#### Statistical analysis

To evaluate the main objective of the study, the reduction in sexual dysfunction achieved by the preservation of the pelvic autonomic nerves, we will use the method based on the one-sided confidence interval at 95% of the difference in sexual dysfunction between the two groups [34, 35], in both the intention to treat and per protocol samples.

The quantitative variables will be described giving values of mean and standard deviation, or medians, interquartile interval and range, as appropriate. The categorical variables will be described in absolute numbers and percentages.

The statistical analysis of the quantitative variables, with independent groups, will be performed with the parametric Student’s T-test, provided that its conditions of application are met; otherwise, the non-parametric Mann-Whitney U test will be used.

In the statistical analysis for categorical variables, the Pearson Χ^2^ test or the Fisher exact test will be used.

These methods will be used to compare the baseline characteristicsof the two groups in order to assess whether the randomization has been effective.

Statistical significance will be set at a *p* value of less than 0.05.

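### The per-protocol set keeps an unspecified part of the control group but all of the IMV-to-IMA group, and the main objective is evaluated in it alongside ITT with no statement of which result carries the conclusion

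*Protocol article*

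**What the plan says.** The section on intention to treat, per protocol and lost patients defines two sets for the comparison of the arms. For the first: "The intention to treat analysis will be applied to all randomized patients". For the second: "The per protocol analysis will include part of the group in which direct dissection of the IMA is performed, and all the group", and the sentence goes on to specify "all the group that undergo dissection from the IMV to the IMA". So the control side is reduced to a part, with no criterion for which part, and the other side is taken whole.

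The Statistical analysis section then says of the main objective: "we will use the method based on the one-sided confidence interval at 95% of the difference in sexual dysfunction between the two groups", to be done "in both the intention to treat and per protocol samples". It does not rank the two sets or say what follows if they disagree.

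The Sample size section specifies "a one-sided hypothesis" at 5% with 90% power, on the basis that "the prevalence of post-TME sexual dysfunction is 50% and intending to reduce the figure to 20" percent. This is a superiority claim.

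**The concern.** A per-protocol set is interpretable only if the same adherence rule is applied to both arms. Here the rule as written selects among controls and names no matching selection on the other side. If the controls who leave differ in prognosis from those who stay, while their counterparts in the IMV-to-IMA group remain, the two groups differ for reasons unrelated to the dissection route. The per-protocol difference can then favour either route when there is no effect.

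This matters because the set is used for the main objective. For a superiority claim the protective analysis is ITT, and the article does not say that the conclusion rests on it. Nor can an analyst build the per-protocol set from the sentence, since nothing identifies the part of the control group to keep. This is not a detail left to an analysis plan: a later document would have to contradict the sentence, not merely complete it.

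**Working it through.** **Inputs from the article.** One-sided 5%, power 90%, 50% versus 20%, 41 patients (a per-arm figure, as the 45 per group after 10% loss shows), 1:1 allocation.

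**The plan's own figure.** With the pooled-variance formula without continuity correction,

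n = [1.645·√(2·0.35·0.65) + 1.282·√(0.5·0.5 + 0.2·0.8)]² / 0.30² = 41.4 per arm.

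This agrees with the stated 41 (42 if rounded up). Power at 41 per arm is 89.7%. The sample size is sound and is not at issue.

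**Inputs that are assumed.** The article gives neither the share f of controls dropped nor their risk. I take no true effect, a rate p = 35% in both arms (midway between 50% and 20%), 41 evaluable per arm, and all 41 kept in the IMV-to-IMA arm. Let g be the risk of retained controls minus the risk of dropped controls.

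**Bias.** The whole control arm has rate p, so f·(r − g) + (1 − f)·r = p, where r is the rate in retained controls. Hence r = p + f·g, and the spurious difference is r − p = f·g.

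**Error.** Chance of a one-sided 5% claim for the IMV-to-IMA route = Φ[(f·g − 1.645·SE₀)/SE₁], with 41(1 − f) controls against 41. SE₀ uses the pooled rate and SE₁ the separate rates.

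Worked case, f = 0.5, g = +20 points: r = 0.45, 20.5 controls, pooled rate (20.5·0.45 + 41·0.35)/61.5 = 0.383, SE₀ = 0.1315, SE₁ = 0.1327. Then (0.10 − 1.645·0.1315)/0.1327 = −0.88, which gives 19.0%.

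| Controls dropped | Gap | Bias (points) | Error, dropped at lower risk | Error, dropped at higher risk |
|---|---|---|---|---|
| 10% | 20 points | 2 | 7.2% | 3.3% |
| 30% | 20 points | 6 | 12.9% | 1.4% |
| 50% | 10 points | 5 | 10.5% | 1.9% |
| 50% | 20 points | 10 | 19.0% | 0.6% |

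Simulation of the 20-point cases with a Wald test (400,000 trials each) gave 7.6% and 3.5% (10% dropped), 13.3% and 1.5% (30%), and 19.2% and 0.7% (50%).

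**Dropping unrelated to outcome (g = 0).** There is no bias, but per-protocol power at 50% versus 20% falls from about 90% to 88%, 84% and 78% with 10%, 30% and 50% dropped (normal approximation). Simulated with 20 controls against 41, it is about 75 to 76%.

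**Effect of the decision rule.** In the same simulations with dropped controls 20 points lower in risk, requiring success in both sets gave an error of 4.9%, 4.8% and 4.7% (10%, 30%, 50% dropped). Accepting success in either set gave 7.8%, 13.5% and 19.7%. With g = 0, accepting either set gave 6.1%, 6.9% and 7.5%.

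**The case against.** The strongest reply is that the randomized comparison is intact. ITT covers all randomized patients and the main objective is evaluated there. That stands: a reader might infer that the trial's randomization is broken, but the article does not support this. Only the per-protocol comparison is exposed.

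A reader might also infer that every patient allocated to the intervention is kept whatever operation was done. The text does not say that. It refers to the group that undergoes the IMV-to-IMA route, so the sentence may be a badly worded treatment-received rule. This limits the charge but does not rescue the set: grouping by route performed is not the randomized comparison either, and the control side is still cut to an unexplained part.

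Third, a reader might infer that the two sets are co-primary and that success in either suffices. That would be reading a rule into silence. Evaluating the objective in both samples may equally mean that both must succeed, and then the error stays below 5% in the cases above. The 19% applies only if the per-protocol result alone can carry the claim.

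Finally, the shares, gaps and 35% rate are assumptions, and the direction is unknown. That also stands.

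One possible explanation for keeping only part of the controls lies in the Surgical technique section. It applies the Melani technique when the splenic angle must be mobilized, before the randomized IMA dissection, and the Background describes that technique as going from the IMV to the IMA. The article does not connect this with the per-protocol set, so it remains a conjecture.

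**Conclusion.** The per-protocol definition is wrong as written. It selects in one arm only, without a criterion, and the resulting set is used for the main objective with no statement of which analysis carries the conclusion. Under the assumptions shown, bias runs from 2 to 10 points, and the per-protocol error from about 0.6% to about 19% against a nominal 5%. These figures illustrate sensitivity; they do not predict what will happen in this trial. Dropping unrelated to outcome would leave no bias and cost power in the per-protocol set only, while ITT power stays about 90%. The finding does not extend to the ITT comparison or the sample size, and it does not rest on an either-set success rule, which the article does not state.

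**What to change.** Replace the per-protocol sentence with one rule for both arms: all randomized patients who received the dissection route they were allocated and have the 12-month assessment. Report exclusions from this set by arm and by reason. State in the Statistical analysis section that the superiority conclusion rests on the ITT analysis and that the per-protocol analysis is supportive. If the Melani step is why only part of the controls was to be kept, the Surgical technique section and the per-protocol definition must be reconciled, so that it is clear what counts as having received the allocated route in each arm.

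The cost is two or three sentences. Sample size, data collection and the planned method of analysis do not change.

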#### Monitoring

Monitoring will be carried out by a data manager. The variables will be recorded on an Access database which the data manager will manage via the various hospitals.

#### Statistical analysis

To evaluate the main objective of the study, the reduction in sexual dysfunction achieved by the preservation of the pelvic autonomic nerves, we will use the method based on the one-sided confidence interval at 95% of the difference in sexual dysfunction between the two groups [34, 35], in both the intention to treat and per protocol samples.

The quantitative variables will be described giving values of mean and standard deviation, or medians, interquartile interval and range, as appropriate. The categorical variables will be described in absolute numbers and percentages.

The statistical analysis of the quantitative variables, with independent groups, will be performed with the parametric Student’s T-test, provided that its conditions of application are met; otherwise, the non-parametric Mann-Whitney U test will be used.

In the statistical analysis for categorical variables, the Pearson Χ^2^ test or the Fisher exact test will be used.

These methods will be used to compare the baseline characteristicsof the two groups in order to assess whether the randomization has been effective.

Statistical significance will be set at a *p* value of less than 0.05.

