## Abstract

**Background:**

Total Mesorectal Excision (TME) is the standard surgical technique for the treatment of rectal cancer. However, rates of sexual dysfunction ofup to 50% have been described after TME, and rates of urinary dysfunction of up to 30%. Although other factors are involved, the main cause of postoperative genitourinary dysfunction is intraoperative injury to the pelvic autonomic nerves. The risk is particularly high in the inferior mesenteric artery (IMA). The aim of this study is to compare pre- and post-TME sexual dysfunction, depending on the surgical approach usedin the inferior mesenteric vessels: either directly on the IMA, or from the inferior mesenteric vein (IMV) to the IMA.

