### Exclusion criteria

Female sex; age under 18; not candidate for neoadjuvant treatment and/or adenocarcinoma > 10 cm from the anal verge candidate to partial TME; abdominoperineal resection (APR); emergency surgery; recurrent tumor; cT4; history of infra-abdominal or pelvic prostate procedures; radiotherapy prior to the current process; patients with severe sexual or urinary dysfunction before surgery; no provision of signed informed consent.

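### Men with non-severe dysfunction before surgery can count as events at 12 months, the primary comparison makes no use of the baseline IIEF-5, and the sample size does not say whether 50% and 20% include such men

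*Protocol article*

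**What the plan says.** - **Eligibility.** Exclusion criteria (protocol article) removes "patients with severe sexual or urinary dysfunction before surgery". No score is attached there. Definitions grades the IIEF-5 as severe at 1–7, moderate at 8–11, mild to moderate at 12–16 and mild at 17–21.
- **Event.** Main variable takes an IIEF-5 of 21 or below as sexual dysfunction, before surgery and at 12 months, with no required change between the two. The urologist decides on the questionnaire and/or penile Doppler, and the Doppler may confirm or overturn the questionnaire result.
- **Baseline.** Trial interventions schedules the functional study, IIEF-5 included, after neoadjuvant treatment and before surgery. The abstract's stated aim is to "compare pre- and post-TME sexual dysfunction" by surgical approach.
- **Allocation.** Description of the randomization specifies simple 1:1 randomization, with no stratification.
- **Primary analysis.** Statistical analysis: "we will use the method based on the one-sided confidence interval at 95% of the difference in sexual dysfunction between the two groups". No baseline term, stratum or new-case definition is named. The one stated use of baseline data is between-group testing, "in order to assess whether the randomization has been effective".
- **Sample size.** "With an α risk of 0.05 (5%), a one-sided hypothesis", 90% power, and "the prevalence of post-TME sexual dysfunction is 50% and intending to reduce the figure to 20" per cent; "it will be necessary to include 41 patients in the two groups" (read here as 41 per group). Then: "Estimating a possible loss to follow-up of 10%, the total sample required will be 90 patients: 45 per group".

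**The concern.** A man who scores 15 before surgery and 15 at 12 months meets the questionnaire criterion for dysfunction whichever vessel was approached first. Such men raise the event rate in both arms and shrink the difference the trial is looking for. How many there are is unknown, but the eligibility rule lets them in.

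The trial measures the variable that would separate these men from new cases, and then gives it no part in the primary comparison. The article's own Discussion, drawing on prostatectomy studies, lists preoperative sexual function among the main determinants of postoperative erectile function. With simple randomization and about 41 evaluable men per arm, the arms can differ noticeably on it by chance, and nothing in the stated analysis corrects for that. Significance tests on baseline characteristics do not fill the gap. Under proper random allocation any difference is due to chance, so a p-value cannot show whether randomization worked, and it adjusts nothing.

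The same ambiguity reaches the sample size, because 50% and 20% mean different things depending on whether pre-existing cases are inside them.

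**Working it through.** **Inputs.** From Sample size: one-sided α = 0.05, power 90%, rates 50% and 20%, 41 per group, 10% loss, 90 in total. From Exclusion criteria, Definitions and Main variable: men at 8–21 are eligible, and the event threshold is 21 or below. The share *b* of enrolled men with dysfunction before surgery is not in the documents. It is an assumption throughout and is shown as a range.

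**1. The plan's own figure.** With p̄ = (p₁ + p₂)/2,

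power = Φ{ [ |p₁ − p₂|·√n − 1.645·√(2p̄(1 − p̄)) ] / √(p₁(1 − p₁) + p₂(1 − p₂)) }.

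For 50% against 20% and n = 41: (1.921 − 1.110)/0.640 = 1.267, so power is 89.7%. The required n per arm is 42 with pooled variance and 40 with unpooled variance. The stated 41 reproduces. For dropout, 41/0.9 = 45.6, against the stated 45, a negligible gap.

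**2. Reading A: 50% and 20% are rates of new dysfunction, and baseline cases persist in both arms.** Total rates are b + (1 − b)·0.5 and b + (1 − b)·0.2. Stratified by baseline, only the 41(1 − b) men per arm free of dysfunction before surgery contribute, at 50% against 20%.

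| b (assumed) | Total rates | Power, no baseline use | Men at risk per arm | Power, stratified | n per arm for 90%, no baseline use |
|---|---|---|---|---|---|
| 10% | 55% vs 28% | 81% | 36.9 | 87% | 56 |
| 20% | 60% vs 36% | 71% | 32.8 | 83% | 73 |
| 30% | 65% vs 44% | 61% | 28.7 | 78% | 95 |
| 40% | 70% vs 52% | 51% | 24.6 | 72% | 124 |

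This assumes full persistence, which is the least favourable case for each b.

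**3. Reading B: 50% is the control total including baseline cases, and the new route prevents only new cases, by the same 60% relative reduction (30/50).** The intervention rate is b + 0.4·(0.5 − b): 26%, 32% and 38% for b = 10%, 20% and 30%. Power at 41 per arm is 73%, 51% and 29%.

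**4. Reading C: 50% and 20% are both total 12-month prevalences in the enrolled men.** Power stays at 89.7%. For the intervention arm to reach 20%, new dysfunction among men free of it at baseline must be (0.20 − b)/(1 − b): 11% at b = 10% and zero at b = 20%. Above b = 20% it cannot be reached unless some baseline cases recover.

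**5. Gain from using baseline when persistence is incomplete.** Assume 90% of baseline cases persist in the control arm and 85% in the intervention arm, with 50% and 20% in the rest. At b = 20%:

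- Total rates: 0.2·0.90 + 0.8·0.50 = 58% and 0.2·0.85 + 0.8·0.20 = 33%.
- Variance term without baseline: 0.58·0.42 + 0.33·0.67 = 0.465.
- Variance term within strata: 0.2·(0.90·0.10 + 0.85·0.15) + 0.8·(0.25 + 0.16) = 0.372.

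The reduction is 20%. The same steps give 26% at b = 30% and 30% at b = 40%.

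**6. Chance imbalance.** With b = 30% in both arms and 41 men each, a gap of 10 points or more means a difference of at least five men (5/41 = 12.2%; 4/41 = 9.8%). Summing the two binomial distributions gives a probability of 28%.

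**The case against.** The strongest reply is that the plan contains no arithmetical error and the comparison is valid. The 41 per group reproduces. The 50% is described as a prevalence after TME, which can be read as a total that already contains pre-existing cases, and power is then about 90%. A reader might infer from the eligibility rule that the 50%-to-20% target and the 90% power are wrong for this endpoint. The documents do not support that: every loss in power above rests on a baseline share they never give. This part of the reply stands.

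Three further points limit the claim.

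- The Doppler clause means that a score of 21 or below is not certainly an event. However, the clause compares nothing with baseline, so it does not make an event a new one.
- A reader might infer that pre-existing cases tell us nothing about the surgical route. That is too strong. Baseline is measured soon after neoadjuvant treatment, and these men may recover or worsen differently by arm.
- Equating the excluded severe dysfunction with IIEF-5 1–7 is an inference from Definitions, though the natural one.

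Finally, covariates are often left to a statistical analysis plan, which is not shown, and the article never uses the word unadjusted. That is fair as far as it goes. But the article does fix the primary method, gives baseline data a different and unsuitable use, and words its aim as a pre-to-post comparison. Clarifying the method and the meaning of 50% and 20% is therefore a comment on what the article states.

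**Conclusion.** The point holds in conditional form. Men with non-severe dysfunction before surgery are eligible and can count as events at 12 months regardless of route, and the stated primary comparison does not use the pre-surgery IIEF-5. Randomization protects against systematic bias, so the consequences are dilution, lost precision and uncorrected chance imbalance.

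The size depends on two things the article leaves open: the share of men with dysfunction at baseline, and whether 50% and 20% include them. If both are total prevalences, power is about 90%. If they are new-dysfunction rates with an assumed 10–40% persistent at baseline, power is about 81–51% without baseline and 87–72% with stratification. A 20% rate is out of reach if more than 20% of men have persistent baseline dysfunction. None of this shows that the stated power is wrong, only that it cannot be confirmed from what is written.

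The case for using baseline does not depend on which reading is right. Under the incomplete-persistence assumptions it cuts the variance by 20–30% for b = 20–40%, using data already collected.

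**What to change.** 1. In Statistical analysis, make the primary analysis the 12-month risk difference between arms, adjusted for or stratified by pre-surgery (post-neoadjuvant) IIEF-5 (above 21 against 21 or below). Keep the one-sided 95% confidence interval.
2. Add new or worsened dysfunction as a supporting analysis, for example a move from above 21 to 21 or below, or a fall of at least one severity class.
3. Present baseline characteristics descriptively, and do not use significance tests to judge whether randomization was effective.
4. In Sample size, state whether 50% and 20% include dysfunction present before surgery, give the baseline share assumed, and restate the power on that basis.

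Items 1 to 3 cost wording only, since the baseline IIEF-5 is already scheduled; they should be settled before any unblinded analysis. Item 4 needs a short recalculation and may give a less favourable power. If 50% and 20% turn out to be new-dysfunction rates and the baseline share is material, stratification recovers part of the loss but does not restore 90%. Under that reading it reaches 83%, 78% and 72% at 20%, 30% and 40%, so the sample size itself would need to be revisited.

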## Discussion

In our study, only men, submitted to TME and candidate for neoadjuvant treatment (chemoradiotherapy) are included, so that the sample is more homogeneous in terms of final results.

TME, performed by minimally invasive surgery through laparoscopic or robotic approaches and/or TaTME, reduces morbidity and accelerates postoperative recovery. Improved quality of life in the medium and long term continues to be one of the main objectives of TME.

Some authors have shown better functional results with the robotic approach due to the superior movements of the wristed instruments that facilitate fine dissection, coupled with a stable and magnified view that helps in recognizing the inferior hypogastric plexus [7]. Due to the lack of experience in robotic surgery and our long experience in laparoscopic surgery, the design of our study has been made only in laparoscopic approach, to avoid the learning curve bias.

It is known, that quality of life and sexual dysfunction rates are not similar among patients submitted to LAR and APR. In our study, only patients submitted to LAR are included, in order to have a more homogeneous sample.

Different definitions of the concept of “quality of life” have been proposed and perhaps no single definition is fully satisfactory. The best one may be: “a state of general satisfaction, derived from the realization of the potential of the person. It has subjective aspects and objective aspects. It is a subjective feeling of physical, psychological and social well-being. It includes, as subjective aspects, intimacy, emotional expression, perceived safety, personal productivity and objective health. As objective aspects, material well-being, harmonious relationships with the physical and social environment and with the community, and health objectively perceived”. As early as 1986, the European Organization for Research and Treatment of Cancer (EORTC) launched a program to assess the quality of life of patients participating in international clinical trials. This is why we have chosen the questionnaire validated by this organization,the EORTC-QLQ C30 [27], to evaluate the quality of life in our study.

Quality of life in our patients is defined by the need for an ostomy orby the presence ofsexual and urinary dysfunctions. Data on these dysfunctions are generally compiled through the use of questionnaires, which all present subjective limitations. As described above, sexual dysfunction is the difficulty at any stage of sexual intercourse (including desire, arousal, orgasm and resolution) that prevents the individual or their partner from enjoying sexual activity [5]. As detailed in the material and methods section, we have followed the indications of the EAU *guidelines (2017)* for the study of sexual dysfunction. The reason for adding the Doppler ultrasound study is to evaluate the cavernous arteries and their spectral evolution, in order to record objective parameters of induced erection and thus to identify the cause of the erectile dysfunction [17]. In addition, there is no reference in the literature of the study of SD in TME with the Doppler and that will give us objective data about it. Clearly, anxiety, psychological strain and any adrenergic stimulus may lead to false positive results, but with the exception of these cases, an altered result can be attributed to a neurogenic cause of erectile dysfunction in patients with a history of nerve damage [36]. Urinary dysfunction is defined as any alteration in the correct functioning in the storage or periodic voiding of urine, either in isolation or simultaneously. The tests used in the study are, once again, the ones recommended in the EAU *guidelines*; however, the only method able to objectively evaluate the presence and type of urinary dysfunction is urodynamic study by means of flowmetry [20].

The rationale for our study is the belief that the dissection routefrom the IMV to the IMA can improve nerve preservation of the nerves. The reason is anatomical, because this approach route follows the plane of dissection of the peritoneal sheets of the retroperitoneum, favoring visualization (and therefore a better preservation) of the pelvic autonomic nerves from their origin.

We hope that our study will show that the approach from the IMV to the IMA can increase the preservation of the pelvic autonomic nerves, and can thuslower the rates of sexual dysfunctionto a figure around 20%.

In parallel, though this is not the objective of our study, we believe that the detection of possible pre-surgical sexual dysfunction can promote prompt treatment of this dysfunction after surgery. Previous studies in the setting of prostate adenocarcinoma surgery have shown that the selection of the patient (according to age and preoperative sexual function, measured with the IIEF), as well as the surgical technique (in the case of radical prostatectomies, the preservation of the neurovascular bundles) are the main determinants of postoperative erectile function [37]. Correct stratification of patients is vital to patient assessment and to the selection of the most appropriate postoperative treatment strategy. These studies conclude that when patients are correctly stratified and selected, a high recovery rate of erectile function can be expected after radical prostatectomy with neurovascular preservation.

If our hypothesis is supported, we believe that the change in approach proposed here will help to improve quality of life in patients undergoing surgery for rectal cancer with neoadjuvant radiotherapy.

